### Monitoring

The trial monitoring plan has been developed and agreed on by the Trial Management Group (TMG) and Trial Steering Committee (TSC). The TMG will meet monthly. The TSC will meet three times over the 24-month project period, with the first meeting taking place prior to the start of study recruitment. The TSC will include members independent from the trial and an independent chair and statistician.

The likelihood of participants being harmed by the interventions in either trial arm is very low. As such, the collection and reporting of AEs in this trial is restricted only to those events that are classified as serious AEs (SAEs). In the context of clinical care and in accordance with local practice, AEs detected by the treating occupational therapists will be recorded in an electronic case report form. PenCTU will immediately notify a research team member (JM) of any reported AEs/SAEs. This team member will then complete an assessment of the causal relationship.

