At monthly intervals throughout the trial, participants will complete a log of falls, resource use and any discomforts they believe to be associated with the OBtAIN-PD study (online or paper-based depending on participant requirements). This log will also collect medication details and any changes to inform analysis, such as introducing anxiolytic medication. The monthly serial collection of data enables the impact of the OBtAIN-PD on these areas to be identified and to assess the suitability of this data collection method, as well as monitor any adverse events (AEs). All patient-reported outcome measures included in this study are validated for use in Parkinson’s disease clinical care and research. The research team designed the falls and resource use log for this study.

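### The protocol limits adverse event collection to serious events, then has non-serious ones recorded too, and its monthly log captures non-fall events only if the participant attributes them to the study

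*Protocol article*

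**What the plan says.** Three statements bear on which safety events the trial gathers.

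- **Serious events only.** Monitoring argues that "The likelihood of participants being harmed by the interventions in either trial arm is very low" and concludes that "the collection and reporting of AEs in this trial is restricted only to those events that are classified as serious AEs (SAEs". The restriction covers collection as well as reporting.
- **Therapist-detected events.** The next sentence of the same section says that "AEs detected by the treating occupational therapists will be recorded in an electronic case report form". It sets no seriousness threshold. The trials unit is then to notify a team member "of any reported AEs/SAEs", and "This team member will then complete an assessment of the causal relationship".
- **Participant log.** Under Secondary outcomes, each month for the whole trial, "participants will complete a log of falls, resource use and any discomforts they believe to be associated with the OBtAIN-PD study". The log also takes medication details and changes. Among its stated purposes is to track changes in these areas "as well as monitor any adverse events (AEs".

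Allocation, concealment and blinding adds that neither participants nor treating therapists can be blinded, and that participants learn their treatment at the first session.

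**The concern.** The first statement excludes non-serious events from collection, the second collects them when a therapist notices them, and the third monitors adverse events of any seriousness through a log. Two teams working from this text could report different events from the same participants.

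There is also a mismatch inside the log. Its purpose covers any adverse event, but apart from falls its only direct question about harm is conditional on the participant's own belief that the study is responsible. Someone who has been given OBtAIN-PD materials and someone receiving usual care may answer that question differently for the same health problem. A difference between arms in logged discomforts could then reflect attribution and not occurrence.

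What is at stake is the safety information handed to the definitive trial. The Background describes people with Parkinson's and higher anxiety as more prone to falling, and the intervention encourages participation in activities. The log is itself one of the data collection methods whose suitability is being tested, so a clear account of what it captures is part of what this feasibility trial has to deliver.

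**Working it through.** No sample size, power or event figure is involved, and the plan gives no number to reproduce. The check sets the three statements side by side and asks which kinds of event each would admit.

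| Event | Serious-only rule (Monitoring) | Therapist route (Monitoring) | Participant log (Secondary outcomes) |
|---|---|---|---|
| Serious event | In | In, if the therapist detects it | In, if it is a fall or an attributed discomfort |
| Non-serious fall | Out | In, if detected | In, whatever the participant thinks caused it |
| Non-serious, non-fall problem that the participant attributes to the study | Out | In, if detected | In |
| Non-serious, non-fall problem that the participant does not attribute to the study | Out | In, if detected | Out as an event, though it may leave a trace in resource use or medication entries |

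1. The first two columns disagree on all three non-serious rows. Both rules stand in the same section, so neither can be set aside as belonging to another process.
2. Treating the therapist route as ordinary clinical recording does not remove the disagreement. The events go into a trial form and lead to notification and a causality assessment, which is collection within the trial.
3. Reading the section as collecting everything but reporting only serious events also fails, because the restricting sentence names collection.
4. The last two rows of the log column differ only in what the participant believes. That belief is formed with knowledge of the treatment, so the chance that a given problem is logged can differ by arm even if its incidence does not. The documents do not give the direction or size of any such difference.
5. Falls carry no attribution condition, so step 4 does not apply to them.

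**The case against.** The best defence is that the three statements do different jobs. An event has to be noticed before it can be classed as serious, so the therapist sentence, which opens by referring to clinical care and local practice, may describe the detection route, with serious events as the reportable set. Falls are a listed outcome in the abstract, so logging them does not in itself breach a serious-only rule. The log's monitoring purpose is one clause among several. The article describes no harms table, the analysis is descriptive, and an agreed monitoring plan and a later SAP may hold the operational detail.

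Part of this stands. Logging falls is not a contradiction, how the log feeds the serious-event process may properly sit elsewhere, and by-arm safety reporting is an inference. But the defence does not explain why collection is restricted and then required, or why notification and causality assessment extend to events not labelled serious. A further document could choose between the statements, but they would still conflict here.

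Three stronger readings are tempting, and the documents do not support them.

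- A reader might infer that non-serious events are captured only during treatment, because sessions run for about 10 weeks of a 24-week follow-up. The remaining 14 weeks (24 − 10) are time without scheduled sessions, and approximate because waits are allowed for. They are not a gap in capture: the monthly log runs throughout, with no arm restriction.
- A reader might infer that falls data are distorted by attribution. The log takes falls unconditionally.
- A reader might infer that causality must be judged with the arm removed, since the person assessing it knows the allocations. Routing such matters to that person follows from keeping the lead researcher blinded, and relatedness is hard to judge without knowing what was received. Masked review is a debatable preference and not a correction of an error.

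**Conclusion.** The point holds as a contradiction in the current text, together with a mismatch between the log's purpose and its content. The plan cannot be followed as written without choosing which events count. The choice changes the reported safety data in every category of non-serious event, and non-fall log events depend on unblinded attribution.

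The consequence cannot be sized in events, because the documents give no rates. It is confined to the interpretation of harms and does not touch the recruitment, retention or completion estimates. It should be fixed but does not threaten the trial's main purpose. The conclusion assumes that safety events will be presented by arm, as the protocol plans for participant-reported outcomes but does not state for adverse events.

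**What to change.** 1. Reconcile Monitoring and the log paragraph of Secondary outcomes into one rule, the same in both arms over the 24 weeks. It should state whether non-serious events are collected, whether they are reported, and from which source. Align the log's stated purpose with what it asks.
2. Specify, before database lock, that therapist-detected and log-detected events are summarised separately by arm. The protocol already commits to signing off a detailed analysis plan by then.
3. For the definitive trial, remove the attribution condition from the log's event question, so that health problems are recorded whether or not the participant thinks the study caused them. Study setting says that recruitment ended in October 2023 and final follow-up is due in April 2024, so in this trial the change could reach only remaining follow-up. It should be made there only if it can be applied equally in both arms, since a partial change would make ascertainment uneven.

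The first two steps cost wording only. The third costs a slightly longer monthly log and a few more entries to process. No new visits are needed.

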## Ethics and dissemination

We obtained ethical approval from our institution’s Faculty of Health Research Ethics and Integrity Committee (Project ID 3757) and the Health Research Authority (REC reference 23/NE/0027). Participants can withdraw from the trial at any time without giving a reason; this will not affect their ongoing or future care. Data will be available on request from the corresponding author on trial completion. We will store data securely on an encrypted institution server. Data will be anonymised before archiving. We will publish the results in a peer-reviewed scientific journal. Participants will receive a summary of the findings at the end of the data analysis. The results will also be published on institution websites, as well as presented at conferences and to professional and patient groups.

### Patient and public involvement

Lay members, including PWPs, care partners and occupational therapists, have provided PPI input. Our PPI has provided input into key aspects of study design. Discussion with our PPI representatives has led the trial to implement the recording of self-report measures via a web-based app to minimise burden and interviewing decliners. PPI representatives will be involved in the development of topic guides for the qualitative component of the trial. In addition, an options appraisal was conducted at the 2022 Royal College of Occupational Therapists annual conference. It was attended by 124 occupational therapists from various clinical backgrounds including (but not exclusively) acute, community, mental health and academic services. Recommendations from this appraisal have been incorporated into this protocol and include the flexibility of treatment session delivery method, competency assessment for the occupational therapists involved in the trial and regular contact/support for the trial occupational therapists in addition to the provided training. A patient advisory group has been recruited to support the research team with patient-relevant advice and guidance on the delivery and progression of the study.
